### Sample size

Previous NHS GG&C studies,^10 21^ combined with internal audit data (showing that 80% of patients have direct or daily smartphone, tablet or web access), indicate that recruitment of 400 participants across a 12-month period is feasible, and likely to provide adequate data to conduct meaningful primary and secondary endpoint analyses.

An improvement in admission-free survival, with reduction in admissions by one per patient per year is projected, if support for provision of evidence-based COPD care is achieved by the service model. As the feasibility of an end-to-end digitalised service model for COPD has not yet been tested, and the service components will be adapted during the study, sample size power calculations and randomisation are not yet appropriate.

### Screening and eligibility assessment

Participants will be identified from ED attendance, hospital admission or COPD multidisciplinary team referral. It is anticipated that the majority of participants will be identified and recruited during their index acute admission.

Review of focused medical history and lung function test results will be undertaken as part of screening evaluation to ensure all inclusion and no exclusion criteria are met.

### Informed consent

We will undertake informed consent with timing which is individualised to be least burdensome and most efficient for participants. Written informed consent will be obtained by participant’s dated signature and dated signature of the person who presented and obtained the informed consent. The person who obtained the consent will be suitably qualified and experienced and have been given authority to do so by the principal investigator (PI).

In addition to consent for the clinical trial, General Data Protection Regulation (GDPR) consent for data sharing, data storage and tracking of web app activity is required, and this is sought within the COPD patient portal when participants complete initial sign-up to the service.

### Withdrawal of subjects

Participants have the right to withdraw from the trial at any point, for any reason, without prejudice to future care. This is clearly stated at time of consent. The investigator can also withdraw participants from the study intervention in the event of protocol violations or if it was felt that involvement in the service was adding unnecessary burden or distress (eg, if participant was approaching end of life). Participant withdrawals will be included within the study analyses and reporting.

Participants may opt to limit the number of interactions—for example, daily questionnaires, that they undergo, if these are burdensome. They may also request ‘conventional’ scheduled face-to-face clinical review rather than remote managed review at any time point. This will be accommodated as outpatient or inpatient attendances, within routine clinical timescales as judged appropriate by the clinical team, in line with current service provision.

### Participant identification

Study numbers will be assigned sequentially as each subject enters the study to ensure that study participant data are de-identified. Corresponding information will be recorded on the Case Report Form (CRF) by the investigator.

### Source data

Source documents will include hospital medical records, clinical charts, laboratory and pharmacy records, radiographs and correspondence. The patient web portal and clinician dashboard will be the source data for clinical summary data, PROs, wearable and NIV physiology, patient–clinician messaging, clinical documentation and exacerbation/admission recording in participants. The clinician dashboard will also output this source data as structured report to NHS GG&C clinical portal (patient EHR).

### Study data

Electronic data and COPD service digital architecture will be held within NHS GG&C e-health systems, with industry standard security and identity assurance processes. The core components of digital service will be on NHS GG&C Azure cloud tenancy, further ensuring security and identity assurance, and avoid need for data de-identification prior to machine learning analysis.

Data access will be password protected and accessible only by study investigators, with data management as per NHS GG&C and NHS Scotland data protection policies. Platform analytics will track user interactions and user data changes, to provide an audit trail for data integrity.

### Subsequent assessments

Participants will be recruited into the digitalised service model over a 12-month period. Observation of secondary endpoints will be continued over the 12-month period following recruitment. Participants who are recruited will subsequently continue within the digital service model beyond the trial period, either until ongoing procurement of the service infrastructure is established, or transition to alternative equivalent service model is completed.

### Definition of end of trial

The end of trial will be when the last participant has completed follow-up, 12 months after recruitment.

### Patient and public involvement

Patients and members of the public were involved throughout the planning and conduct of this research. The patient-facing web portal which forms the basis of the study was co-designed with patients with COPD and their carers. Semistructured interviews were conducted between patients and the development team to understand patient experience of their condition, with feedback and adaptation of the application at each development stage. Subsequent development of research questions and study design was informed by insights gained through these interactions.

### Study limitations

We recognise that there is an inherent risk of bias and limitations to using this type of study design with regard to the conclusions that can be drawn from the study outcomes. With this acknowledgement, our study seeks to explore the feasibility of using this digital service model within a real-world setting as opposed to providing evidence of definitive proof or utility. If feasibility is established, the format and experience gained from conducting this initial research will form the basis for future randomised studies.

## Data collection

### Data collection by research team

#### EHR data

The following data will be obtained from EHRs held within NHS GG&C SafeHaven: demographic, coded diagnosis list, Charlson Comorbidity Index, Scottish Index of Multiple Deprivation quintile, medication history, laboratory results, lung function results, ED attendance, hospital admission, pulmonary rehabilitation attendance data from 1 January 2010 onwards. These data will be presented for evaluation in a study machine learning analysis platform.

#### Baseline clinical data

The following data will be collated when the participant is enrolled and added to the clinical details form visible on the clinician dashboard: participant age, sex, smoking status, vaccination status, comorbidities, COPD exacerbation history, COPD medications, lung function results, key laboratory results including maximal eosinophil count and modelled home pollution exposure (QCumber platform; NO2, O3, PM2.5, black carbon).

Participants who have not had contemporary spirometry (standard lung function test) will have this repeated at the time of recruitment—this would be routine clinical care.

#### Follow-up clinical data

Smoking cessation, vaccination status, pulmonary rehabilitation, COPD comorbidity, COPD exacerbation history, COPD medications and other treatments, inhaler technique and narrative history will be updated at clinical encounters, as relevant.

A data feed from NHS GG&C Trakcare platform to RECEIVER Study COPD platform will present information on hospital attendance and admissions.

Clinical episodes are also captured in the weekly PRO questionnaires, and manually inputted by the clinical team, when these are noted.

Accuracy of coding of clinical summary data and clinical episodes will be reviewed in a proportion of recruited participants, by a respiratory physician working independent of this study.

#### Physiology substudy

A subset of participants (where time and mode of presentation allow) will be offered recruitment to the exploratory physiology substudy and have additional physiology measurements taken. These will comprise of oscillometry, parasternal EMG and home air pollution pack monitoring. Measurements from these may predict/associate with stability of COPD and clinical endpoints, and follow-up measurements may be taken at 3, 6, 9 and 12 months if feasible during study, alongside routine clinical care. The principal purpose of conducting these in this study is to report on feasibility within routine COPD assessment.

### Data from PROs

Participants (or their family or carer) will complete PRO questionnaires in the patient web portal. Daily SMS and/or email notifications are provided as a prompt to complete these. There is support information in the associated website to assist participants with any difficulties with the patient portal. Additional support will be provided by the clinical users if required.

Participants will complete symptom diary and COPD assessment tool (CAT) questionnaire daily. Medical Research Council dyspnea score (MRC) and healthcare episode questionnaires will be completed weekly. EQ-5D-5L generic quality of life questionnaire will be completed every 4 weeks. These questionnaires have been integrated to improve question flow and simplify the user experience. Questionnaire flow content is included in the online supplemental material 1.

10.1136/bmjresp-2021-000905.supp1Supplementary data

PRO data are presented unmodified, in a ‘user-friendly’ format (co-designed with clinical users), in the clinician dashboard. These unmodified data will inform and enhance clinical encounters and patient–clinician communication.

Pilot user experience research shows that the daily PRO questions can be completed in ~70 s, with weekly questions taking an additional 90 s, and monthly generic quality of life questions taking an additional 5 min.

Specific permission for use of CAT questionnaire within this e-health system has been obtained. The use of other PROs is covered by available open licensing.

### Wearable physiology measurement

Participants will be provided with a Fitbit Charge 3 wristband wearable device, to monitor activity, sleep, heart rate and energy expenditure variables.

Wearable physiology results and device support instructions will be available to participants in the Fitbit app.

Wearable physiology results are presented unmodified in the clinical dashboard, to inform and enhance clinical encounters and patient–clinician communication.

### Remote-monitored home NIV

Participants with severe COPD who have standard indications (persistent hypercapnia with PCO_2_ >7 kPa and/or recurrent episodes of acute hypercapnic respiratory failure and/or COPD–obstructive sleep apnoea overlap and/or COPD with significant nocturnal hypoventilation) are commenced on home NIV in NHS GG&C using Resmed Lumis 150 ST-A device as routine clinical care. Participants with significant obstructive sleep apnoea syndrome may be alternatively commenced or transitioned to auto-titrating continuous positive airway pressure (CPAP) using an AirSense-10 device. NIV initiation and optimisation will be conducted as per standard NHS GG&C clinical protocol. NIV data capture and device adjustment will be via ResMed AirView platform, again as routine clinical care.

AirView data will be acquired via an open application programming interface (API) to the COPD platform and presented in the clinical dashboard, to improve data visualisation for NIV clinical management alongside PROs and wearable data, and to inform and enhance other clinical encounters and patient–clinician communication.

### Patient portal support materials, care plans and clinical decision support

The patient web portal will contain linked content to NHS GG&C smoking cessation, vaccination, inhaler therapy, pulmonary rehabilitation, breathing control and ‘my lungs, my life’ COPD support literature, all to aid self-management.

The patient resource within the patient portal will contain a structured exacerbation self-management care plan. This is a digitalised version of the paper structured self-management plan without any change in format or content. Participants will be empowered to activate their own self-management plan or supported/directed to activate this with patient–clinician communication, as standard routine clinical care: the data access, visualisation and patient–clinician messaging facilities in this study will however enhance this.

### Machine learning analysis and predictive modelling

These analyses will be conducted post hoc, using the clinical data obtained from the RECEIVER trial COPD platforms, alongside EHR data in historical and contemporary control patients from NHS GG&C SafeHaven. The anticipation is that following analysis of the study data, we will be able to judge the feasibility and accuracy of using predictive model outputs at a service or individual patient level. This may lead to the subsequent development and evaluation of artificial intelligence(AI)-based clinical decision support tools. Relevant clinical investigation/medical device trial(s) of these would be proposed and designed. The data from the RECEIVER trial would not be used directly to support clinical validation of any subsequently developed medical device.

### Service model iterations

The components of the RECEIVER service model have been subject to pilot evaluation and pretrial patient and clinical user experience research. Service refinement based on the clinical user substudy experience research will continue during pretrial preparation and approval period. Iterations of the digital service content (eg, rationalisation of patient outcomes, modification or addition of self-management support materials) based on the adoption experience will be considered by the project steering group at three monthly intervals during the study. Where this iteration would result in a change in the clinical protocol, this will be submitted as an amendment for consideration and regulatory approval before any change is implemented.

## Study outcome measures

Primary and secondary endpoints for the RECEIVER Study are shown in table 1.

**Table 1 T1:** RECEIVER primary and secondary endpoints

Primary endpoint	Proportion of enrolled high-risk participants with COPD who use remote management in a digital service model
Secondary endpoints	Clinical outcomes, comparing impact of digitally enabled remote management versus historical and contemporary SafeHaven cohorts: Clinical events: COPD exacerbation; unscheduled care contact (digital platform, COPD team visit, primary care, emergency department, hospital admission); mortality—COPD and non-COPD related. Hospital occupied bed days preceding and subsequent 12 months (adjusted time interval if survival <12 months). Treatment uptake (where indicated): smoking cessation; pulmonary rehabilitation; vaccination; supported self-management; home oxygen; home NIV. NIV group: NIV usage, symptom change, NIV therapy parameters, blood gases during routine clinical care. Supported self-management: utilisation of self-management information (page views), number of exacerbation managed at home versus in hospital, number of rescue packs used in 12 months (captured through weekly PROs), utilisation of messaging (number of message threads), sputum microbiology (where available during routine clinical care), impact of patient activation measures (where measured during routine care). Impact of demographics, physiology and patient activation measures (where measured during routine care)—deprivation category of area of residence, age and sex, number of previous admissions, smoking status, participation in pulmonary rehabilitation in previous 2 years; lung function measurements, modelled home air pollution exposure; EMG, oscillometry and home air pollution monitoring in subset of participants where this is carried out—on outcomes, clinical events and treatment uptake. Clinical service outcomes for digital service model, remote-managed home NIV and supported self-management: Remote-managed home NIV: number, nature and complexity of NIV therapy reviews and interventions to provide. Supported self-management: number, nature and complexity of reviews and interventions to provide. Digitalised service model: user and developer time/cost required for development and modification of clinical dashboard; qualitative analysis (clinical user satisfaction and reflection on efficiency or additional workload); quantitative analysis (clinical dashboard utilisation tracking). Patient portal: user and developer time/cost required for development and modification of clinical dashboard; qualitative analysis (user satisfaction) and quantitative analysis (uptake, engagement with app and wearable, successful use of digital service vs bypass to conventional healthcare contacts). Machine learning-supported exploratory analyses of associations and relative predictive importance of electronic health record, PROs, wearable physiology and NIV parameters: Associations between changes in PROs (MRC, CAT, symptom diary, and EQ-5D-5L questionnaires) with routine clinical care interventions, COPD exacerbation and other clinical events. Associations between changes in wearable monitoring parameters (activity, sleep, heart rate variability, energy expenditure, respiratory rate) with routine clinical care interventions, COPD exacerbation and other clinical events. Associations between changes in NIV-monitored parameters (usage, leak, airway pressures, respiratory rate, tidal volume, minute ventilation, inspiratory/expiratory ratio and detected respiratory events) with routine clinical care treatment interventions, COPD exacerbation and other clinical events. Associations between changes in clinical endpoints and relative importance plots of all remote management-acquired data (including EMG, oscillometry and home pollution monitoring exploratory endpoints in subgroup these measured on) to determine contribution of these to outcome prediction, and therefore value of these for future prospective study. Patient-centred outcomes: Health-related quality of life (EQ-5D-5L) at baseline and monthly during study. Qualitative user research (planned subset of participants, convenience sample) with semistructured user experience interviews. Impact of patient activation (where this is measured at baseline and/or follow-up during routine clinical care) on enrolment and use of digital service model. Healthcare cost analyses: Development and installation costs for digitalised service model for remote management of COPD. Recurring costs (clinical staffing, digital platform hosting, digital platform scheduled update and maintenance) for digital service model for remote management of COPD. Projected direct and indirect cost-savings (admission and unscheduled care reduction, travel, carer burden impact, clinical efficiency) of high-risk COPD with digitally enabled remote management, compared with previous service model.

CAT, Chronic obstructive pulmonary disease assessment tool; COPD, chronic obstructive pulmonary disease; EMG, Electromyography; MRC, Medical Research Council dyspnea scale; NIV, non-invasive ventilation; PROs, patient-reported outcomes; RECEIVER, Remote-Management of COPD: Evaluating the Implementation of Digital Innovation to Enable Routine Care.

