## Statistics and data analysis

Secondary outcomes in the RECEIVER observational cohort will be compared with matched retrospective data from de-identified linked datasets of historical control and contemporary control high-risk patients with COPD. These will comprise of patients identified from coding and admission data as having had severe exacerbation of COPD between 1 January 2010 and 30 April 2019 (historical cohort) and between 1 July 2019 and 30 June 2020, excluding participants enrolled in the RECEIVER Study (contemporary control). The historical control dataset will contribute to machine learning models development. Secondary outcome analysis will be separately compared between the RECEIVER cohort, historical cohort and contemporary control cohort. This component of the study is also separately registered with dataset access approval from NHS GG&C SafeHaven LPAC.

The clinical endpoint data will be reported as a proportion and 95% CI for that outcome, calculated by Kaplan-Meier method. Demographic data will be presented as mean and SDs, or medians and IQRs as appropriate. Correlation, t-test, analysis of variance and effect size analyses will be used as appropriate for secondary endpoint analysis, comparing results of clinical endpoint and patient-centred outcomes with NIV therapy and supported self-management parameters.

Machine learning ensemble methods will be used to develop binary classification problems for patient risk. Precision, recall, accuracy and C-statistics of the receiver operating characteristic curve will be used to evaluate model performance.

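### Table 1 compares exacerbations, unscheduled contacts and treatment uptake with SafeHaven controls, but several components have extra recording routes in RECEIVER and no listed control source, so differences may partly or wholly reflect recording

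*Protocol article*

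**What the plan says.** **The comparison.** Table 1 (Study outcome measures) opens the secondary endpoints with "Clinical outcomes, comparing impact of digitally enabled remote management versus historical and contemporary SafeHaven cohorts". Under that heading come COPD exacerbation, "unscheduled care contact (digital platform, COPD team visit, primary care, emergency department, hospital admission", mortality, bed days, and treatment uptake: "smoking cessation; pulmonary rehabilitation; vaccination; supported self-management; home oxygen; home NIV". The section Statistics and data analysis repeats the intention: "Secondary outcomes in the RECEIVER observational cohort will be compared with matched retrospective data".

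**Recording in RECEIVER.** Source data makes the patient portal and clinician dashboard the source for, among other things, "clinical documentation and exacerbation/admission recording in participants". Follow-up clinical data adds a Trakcare feed of attendances and admissions, and then: "Clinical episodes are also captured in the weekly PRO questionnaires, and manually inputted by the clinical team, when these are noted". Treatment items are refreshed at visits; that sentence ends "inhaler technique and narrative history will be updated at clinical encounters, as relevant". Secondary endpoint measures also names a weekly SafeHaven export and platform tracking.

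**Recording in controls.** Statistics and data analysis describes retrospective, de-identified linked datasets of patients found through coding and admissions. The SafeHaven fields listed under EHR data are demographics, coded diagnoses, comorbidity and deprivation indices, medication, laboratory and lung function results, and "ED attendance, hospital admission, pulmonary rehabilitation attendance data from 1 January 2010 onwards".

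**The concern.** A between-cohort difference can be read as a service effect only if an event has a similar chance of being recorded in each cohort. Here one cohort is asked about healthcare episodes every week and has clinicians adding entries, while the other is seen only through routine linked data. Nothing in the article limits the contrast to components recorded the same way in both.

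The direction depends on the outcome. Fuller recording in RECEIVER raises its counts of exacerbations and contacts, which works against the service. It also raises recorded treatment uptake, which works in its favour. A benefit could therefore be hidden on one endpoint and manufactured on another in the same report. Table 1 also plans projected savings from fewer unscheduled contacts compared with the previous service model, so the problem could carry into the cost analysis.

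**Working it through.** **Step 1: match each component to its stated sources.**

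| Component in Table 1 | Recorded in RECEIVER by | In the SafeHaven fields listed under EHR data? |
|---|---|---|
| ED attendance, admission, and exacerbations leading to either | Trakcare and SafeHaven feeds, plus portal, weekly questionnaire and clinician entry | Yes |
| Rehabilitation attendance | SafeHaven export, plus updates at encounters | Yes |
| Exacerbations managed at home | Weekly questionnaire, clinician entry | No |
| Primary care and COPD-team contacts | Weekly questionnaire, clinician entry | No |
| Vaccination, smoking cessation, supported self-management, home oxygen, home NIV | Dashboard, encounters, platform | No |
| Platform contacts, page views, message threads, rescue packs reported by questionnaire | Platform and questionnaires | No control counterpart |
| Death | Clinical event data | Not listed; linkage to be confirmed |

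The first two rows can be compared if the same routine source is used for both cohorts. The next three have a RECEIVER recording route and no listed control source. The only check on recording quality, the independent review in Follow-up clinical data, covers recruited participants, so it cannot measure under-recording in controls.

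**Step 2: size for a contact rate.** The plan gives no figure to reproduce; Sample size declines a power calculation. All inputs here are assumptions. Let *h* be the share of true contacts that are ED attendances or admissions, recorded in both cohorts, and *c* the fraction of the remaining contacts recorded in controls. RECEIVER is taken to record everything and the true rates are equal. Then

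apparent rate ratio = 1 / [*h* + (1 − *h*)*c*]

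| *h* | *c* = 0 | *c* = 0.5 |
|---|---|---|
| 0.3 | 1/0.30 = 3.33 | 1/0.65 = 1.54 |
| 0.5 | 1/0.50 = 2.00 | 1/0.75 = 1.33 |
| 0.7 | 1/0.70 = 1.43 | 1/0.85 = 1.18 |

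**Step 3: size for a proportion.** Assume a true proportion of 50% in both cohorts, 95% of events recorded in RECEIVER, and an unmatched comparison of 400 with 400 at two-sided 5%. The 400 is the planned recruitment; the control number is assumed. The spurious difference is 0.5 × (0.95 − control capture).

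- Control capture 90%: 47.5% against 45.0%, 2.5 points; chance of a significant result in that direction about 11%.
- Control capture 80%: 47.5% against 40.0%, 7.5 points; 57%.
- Control capture 70%: 47.5% against 35.0%, 12.5 points; 95%.

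**Step 4: after restriction.** If only ED attendances and admissions from the same routine source are counted, *h* = 1 and the ratio is 1/1 = 1.00 when there is no true effect.

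**The case against.** Several counter-arguments have weight.

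- *RECEIVER does not rely on portal and clinician entry alone.* This stands. Secondary endpoint measures gives it a SafeHaven export and a Trakcare feed, so same-source data already exist for participants. But the article does not say that the contrasts will use only those feeds, and Source data points to the portal and dashboard.
- *The field list may not describe the control extract.* This stands in part. EHR data ties the list to the machine learning platform, and the control component is registered separately in a document not shown. Absence is therefore inferred. The same caution applies to mortality, which the list also omits.
- *Platform contacts are a true zero in controls.* This stands: it is a feature of the service and not a recording gap. It still means that a total including them does not compare like with like.
- *The Table 1 heading cannot sensibly apply to every item below it*, since page views plainly have no control value. That is reasonable for those items, but exacerbation, contacts and uptake are the natural content of the comparison.
- *The stakes are limited.* These are secondary endpoints, and Study limitations disclaims definitive proof. That lowers the severity; but the statement there is general and does not name differential recording.

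A reader might go further and infer that every difference on these outcomes will be an artefact, or that exacerbations will appear 2 to 5 times as frequent in RECEIVER (1/0.5 to 1/0.2, if routine coding caught 50% down to 20% of them). The document supports neither. ED attendance, admission and rehabilitation attendance are listed for SafeHaven, so part of each endpoint is comparable. No capture fraction is given, and the 2-to-5 figure needs complete recording in RECEIVER, although participants may opt for fewer questionnaires (Withdrawal of subjects).

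**Conclusion.** The point holds for specific components. On the sources this article lists, contrasts with controls on primary care and COPD-team contacts, home-managed exacerbations, and every uptake item except rehabilitation may partly or wholly reflect recording. Platform contacts, page views, message threads and questionnaire-reported rescue packs have no control counterpart. ED attendance and admission, the exacerbations leading to either, and rehabilitation attendance can be compared, provided one routine source serves both cohorts.

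The size cannot be derived from the document. The apparent ratios of 3.33 to 1.43 and 1.54 to 1.18 illustrate the order of magnitude under assumed contact shares, complete RECEIVER recording and no true effect. They would shrink if SafeHaven holds fields that the article does not list, or if RECEIVER recording is incomplete. The primary endpoint is unaffected. The change is worth making because these outcomes are intended to show clinical impact.

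**What to change.** In Table 1 and in Statistics and data analysis:

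1. Limit the contrasts with historical and contemporary controls to outcomes drawn from the same routine source in both cohorts: ED attendance, admission, exacerbations leading to either, occupied bed days, rehabilitation attendance, all-cause mortality if linkage is confirmed, and any other field confirmed to be in the extract for both cohorts.
2. State that for these contrasts the RECEIVER values also come from that source, and not from platform, questionnaire or clinician entries.
3. Report the remaining components as descriptive results for RECEIVER only.

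For the listed fields this is a wording change that needs no new data, since participants already have the SafeHaven export. The cost is that fewer secondary outcomes carry a control comparison.
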